### Clinical effectiveness: outcome measures

Clinical effectiveness will be evaluated posttreatment (at 4 months) and at 8- and 12-month follow-ups by trained independent evaluators not associated with other aspects of the study. Assessment measures were selected to evaluate both physical and emotional health constructs related to COPD/HF patient-centered outcomes (Chronic Respiratory Questionnaire
[54], Kansas City Cardiomyopathy Questionnaire
[55]), anxiety
[56], and depression (Patient Health Questionnaire-9 (PHQ-9)
[57]). These effectiveness measures have strong psychometric properties and possess a high degree of external validity for clinical use in the primary care setting. For example, within the VA, the PHQ-9 is the standard measure for depression screening and intervention outcome evaluation
[58]. Other study variables include demographic variables, COPD/HF severity, presence/absence of coexistent psychiatric and medical conditions, psychotropic medication use, and health-services use, including ambulatory and inpatient care, primary care, and specialty care. Treatment intensity (“dose”) will be measured by total number of bCBT sessions.

In addition to the above quantitative measures, semistructured-interview data are being collected from patients and providers regarding the impact of the intervention on physical and emotional health and identification of salient aspects of the treatment. Interviews will be conducted with all enrolled clinicians and a purposeful sample of 5 to 10 patients identified during the later stages of the trial. Patients are selected based on ACCESS clinician recommendations. Clinicians also refer ACCESS patients who recently completed treatment and might be able to share additional information about the intervention (whether positive or negative and regardless of treatment engagement).

### Clinical effectiveness: analyses

All quantitative analyses will be done on an intention-to-treat basis, and participants will be analyzed in the group to which they were randomized. Absolute differences in outcome measures will be examined between baseline and 12-month follow-up, and the effect sizes of the bCBT group will be compared with those of participants in the UC group. We will also examine effect sizes for the bCBT group baseline versus posttreatment and eight-month follow-up. To compare changes between the two groups over time, we will use longitudinal, mixed-model analyses that allow nesting of patients by medical center site.

Qualitative data will be collected using audiotaped interactions of the semistructured interview, transcribed and coded for themes, in combination with interviewer (field) notes. Using content-analysis methods, we will code textual data from the patients’ and providers’ perspectives to uncover patterns in the experiences of the bCBT intervention
[59-62]. Coding and analysis will be conducted using formal qualitative-research methods. It is anticipated that qualitative data will provide details about the meaning of the intervention and its context within primary care that are unattainable using survey methods.

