### Identification and recruitment of participants

Study participants are being recruited from the Houston and Oklahoma City VA medical centers, using VA administrative databases to identify COPD and HF patients who received care in the prior year. Houston and Oklahoma City VAs were chosen for their size and integration of primary care mental health within the Veterans Integrated Service Network 16. Opt-out letters are mailed to participants to ensure the widest catchment possible. Interested participants complete a telephone screening process. Participants are included in the study if they are confirmed to have patient-reported functional limitations associated with their COPD and/or HF and have clinically significant symptoms of anxiety and/or depression. Participants are excluded only for clinical factors (*e.g.*, ongoing psychotherapy, concurrent specialty mental healthcare) or patient factors (*e.g.*, cognitive, bipolar, psychotic, or substance use disorders) that would render a PC-MHI bCBT intervention or PC-MHI treatment setting inappropriate
[51]. Patients receiving psychotropic medications are not excluded, although they have their medication use monitored during the course of the study.

Sample size was established to ensure adequate power to detect differences in the primary patient outcomes for depression, anxiety, and physical health. To ensure 80% power to detect differences at the 0.05 level for all study measures, adjusting for repeated measures, a sample size of 180 randomized patients was necessary. However, this sample-size calculation was inflated because of the potential for intraclass correlations related to the clustering of patients within bCBT providers. Using an established inflation factor
[52] and controlling for attrition of 25%, the final sample-size calculation required 200 participants for the ACCESS arm and 120 for UC (320 total). Unequal randomization, an accepted practice in clinical trials

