[53], was used to reduce unnecessary recruitment without significant impact on power. Randomization was stratified by medical condition (COPD only, HF only, both COPD and HF) and by site, using random block sizes of 5 or 10. Because of the higher number of patients in Houston, 200 of the 320 total patients will be randomized at Houston and 120 at Oklahoma City. Random allocation lists were generated using SAS statistical software (SAS Institute, Inc., Cary, NC, USA). Randomization numbers are drawn from envelopes stuffed by non-project staff and opened only after a participant is deemed fully eligible and ready for group assignment.

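### The effectiveness comparison is framed as change from baseline and the model names only site; state how the baseline score and the medical-condition stratum enter, because a comparison of changes with free baseline means gives up precision

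*Protocol article*

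**What the plan says.** The section *Clinical effectiveness: analyses* describes two pieces of work.

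- An effect-size comparison: "Absolute differences in outcome measures will be examined between baseline and 12-month follow-up", with the effect sizes of the two arms then compared.
- A model-based comparison: "To compare changes between the two groups over time", a longitudinal mixed model with patients nested in medical center site.

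Neither sentence mentions adjustment for the baseline score, and neither says whether baseline is a response, a covariate or held equal across arms.

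Under *Identification and recruitment of participants* the article states: "Randomization was stratified by medical condition (COPD only, HF only, both COPD and HF". The second stratification factor is site, and of the two only site reappears in the description of the model.

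The sample-size paragraph in the same section sets its target in these words: "To ensure 80% power to detect differences at the 0.05 level for all study measures, adjusting for repeated measures". The number it arrives at before inflation is 180. That number is then raised for clustering within therapists and for 25% attrition, to 200 ACCESS and 120 usual-care patients. It does not say whether the variance behind the 80% is that of a change, of a baseline-adjusted score or of something else.

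**The concern.** Both analysis sentences point to a comparison of within-patient changes. In a randomized trial the arms have the same expected baseline, so the difference in change and the baseline-adjusted difference at follow-up estimate the same treatment effect. They differ in precision. A change score subtracts the whole baseline value, measurement noise included; adjustment subtracts only the part that predicts follow-up. In large samples adjustment is never the less precise of the two. A change score also carries any chance baseline difference between arms into the estimate of the one trial that is run, even though it is right on average.

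With a planned power of 80%, this choice can matter for every effectiveness outcome.

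The stratum is the lesser part. Leaving a stratification factor out of the model tends to make standard errors conservative when the factor predicts the outcome. The Chronic Respiratory Questionnaire and the Kansas City Cardiomyopathy Questionnaire are disease-specific, so a relation with condition is plausible for them.

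**Working it through.** **Inputs from the article.** Alpha 0.05 (two-sided assumed), power 80%, 180 patients before inflation, 25% attrition, 200 and 120 after inflation, visits at 4, 8 and 12 months.

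**Inputs not in the article, assumed here.** Baseline to follow-up correlation r, the ratio k of baseline SD to follow-up SD, and the share R² of outcome variance explained by the condition stratum.

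**The plan's own figure.** If 180 means 90 per arm, then 90/0.75 = 120, which is the usual-care arm. For ACCESS, 200 × 0.75 = 150 completers, and 150/90 = 1.67 is the design effect this implies. With 90 per arm, 80% power corresponds to a standardized difference of (1.960 + 0.842) × √(2/90) ≈ 0.42. The 320 is therefore arithmetically consistent, but it cannot be rebuilt independently: effect size, SD, correlation, intraclass correlation and inflation factor are not given.

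**Change against baseline adjustment, equal SDs.** Per patient, with outcome variance σ²:

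- change score: 2σ²(1 − r)
- baseline-adjusted: σ²(1 − r²)
- ratio: (1 − r²)/[2(1 − r)] = (1 + r)/2

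The power columns use Φ(2.802 × c − 1.960), with c = 1/√ratio in the third column and c = √ratio in the last.

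| r (assumed) | Variance ratio | If the 80% refers to change: power after adjustment | Patients replacing the 180 | If the 80% refers to adjustment: power when changes are analysed |
|---|---|---|---|---|
| 0.3 | 0.65 | 93.5% | 117 | about 62% |
| 0.5 | 0.75 | 89.9% | 135 | about 68% |
| 0.7 | 0.85 | 86.0% | 153 | about 73% |

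**Does the mixed model escape this?** A generalized least squares calculation with four visits, compound symmetry and 150 and 90 completers gives the variance of the 12-month contrast in change:

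| r | Free baseline means | Baseline means held equal | Ratio |
|---|---|---|---|
| 0.3 | 0.02489 | 0.01618 | 0.65 |
| 0.5 | 0.01778 | 0.01333 | 0.75 |
| 0.7 | 0.01067 | 0.00907 | 0.85 |

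The free-means variance is exactly that of the change score: at r = 0.5, 2(1 − 0.5)(1/150 + 1/90) = 0.01778. Being a mixed model does not by itself recover the precision; constraining or adjusting for baseline does.

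**Unequal SDs.** Patients must have clinically significant anxiety and/or depression to enter, which may narrow the baseline spread of those scores. With baseline SD = k × follow-up SD, the ratio is (1 − r²)/(1 + k² − 2kr). At r = 0.5:

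- k = 1: 0.75/1.00 = 0.75; change needs 1/0.75 = 1.33 times the patients
- k = 0.8: 0.75/0.84 = 0.89; 1.12 times
- k = 0.7: 0.75/0.79 = 0.95; 1.05 times

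The difference in variance, change minus adjusted, is (σ₀ − rσ₁)², where σ₀ is the baseline SD and σ₁ the follow-up SD. It is never negative, so the direction does not depend on the assumptions; the size does.

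**Condition stratum.** Multiplying the variance by (1 − R²) moves 80% power to 80.4%, 80.8%, 82.0% and 84.0% at R² = 1%, 2%, 5% and 10%. If the outcome is change, a constant difference between conditions cancels within patients, and the relevant R² is only that for change itself.

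**The case against.** The strongest reply is that much of this is read from silence. The article is condensed, it gives one sentence on the model, and covariate lists are commonly left to an analysis plan, which is not at hand. Naming site as the nesting level does not exclude a fixed effect for condition. Comparing changes over time is also ordinary wording for a group-by-time model, and such a model can be fitted with baseline means held equal. Table 1 puts the effectiveness objective as superiority on scores at the end of treatment and at the two later follow-ups, which fits a baseline-adjusted analysis equally well.

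This stands against the stronger readings. A reader might infer that the outcomes will be analysed as raw change scores and that the condition stratum has been left out. The documents do not show either: the sentence on absolute differences describes an effect-size comparison, the test between arms belongs to the mixed model, and no covariate list is given. Nor do they support reading the comparison as biased, or the trial as falling short of its planned power: changes are unbiased under randomization, and the variance basis of the 80% is not stated.

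It is also fair that the size of the loss is not in the documents, that (1 + r)/2 needs equal SDs, and that the stratum is worth only about 0 to 4 power points over R² from 0 to 10%.

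What the reply does not remove is that the article does make a choice. It twice frames the comparison as change and names one of two stratification factors. Fitted in the direct way, with free baseline means, that model has the change-score variance, and nothing in the text supplies the adjustment.

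**Conclusion.** The point holds as a conditional one about efficiency. If the comparison is fitted as changes with free baseline means, its variance exceeds that of a baseline-adjusted analysis; the adjusted variance is 0.65 to 0.85 of it for assumed r from 0.3 to 0.7 with equal SDs, and about 0.89 at r = 0.5 if the baseline SD is 0.8 of the follow-up SD. If baseline is adjusted for or constrained, the loss is zero. The direction holds in large samples for any r and any SDs; the size rests on values the article does not give. Including the condition stratum matches the analysis to the randomization but probably adds little precision. The plan should be clarified on both, with more weight on the baseline score.

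**What to change.** State that the mixed model takes the 4-, 8- and 12-month scores as outcomes, with treatment by visit as the effect of interest and baseline score by visit as covariate. A longitudinal model that includes baseline as a response with means constrained equal across arms is an equivalent choice. Add fixed effects for medical-condition stratum and site. Where an outcome is analysed only in patients with one of the diseases, keep the condition levels that remain. The baseline-to-12-month differences can stay as descriptive summaries by arm.

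The cost is a few lines of analysis text and a few degrees of freedom in a trial of 320. No new data are needed: the planned differences already require baseline scores, and the strata are known at randomization. Settle the wording before anyone sees outcomes by arm, so that the choice between change and adjustment cannot follow the results.

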### ACCESS clinicians

The study has targeted the inclusion of 12 PC-MHI clinicians between the two sites. The project team is working collaboratively with local stakeholders and clinic directors to identify clinicians best suited to provide psychotherapy services. Clinician enrollment is not influenced by prior psychotherapy or CBT knowledge and skill. However, clinicians are expected to have an interest in using bCBT in their daily practice and are asked to voluntarily participate and formally consent to participate. Nurses, social workers, psychologists, counselors, nurse practitioners, and physician assistants will potentially be included in the trial. Pretrial data will be collected for all study providers to help identify unequal entry-level bCBT expertise in care providers. Follow-up fidelity data will be collected throughout the project to document provider skill and intervention adherence.

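### The sample size allows for clustering of patients within bCBT clinicians, but the only between-group model over time names nesting by the two sites and no clinician level

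*Protocol article*

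**What the plan says.** In *Clinical effectiveness: analyses*, the between-group comparison over time is given in one sentence: "we will use longitudinal, mixed-model analyses that allow nesting of patients by medical center site". The same section makes the analysis intention-to-treat.

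In *Identification and recruitment of participants*, the planning starts from this aim: "To ensure 80% power to detect differences at the 0.05 level for all study measures". Before inflation, "a sample size of 180 randomized patients was necessary". The text then explains that "this sample-size calculation was inflated because of the potential for intraclass correlations related to the clustering of patients within bCBT providers". The size of that adjustment is cited but not given ("Using an established inflation factor"). After a further allowance for 25% attrition, the result is 200 patients for bCBT and 120 for usual care.

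In *ACCESS clinicians*: "The study has targeted the inclusion of 12 PC-MHI clinicians between the two sites".

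Clinician also appears in *Implementation evaluation plan and analyses*, where engagement and adherence rates are compared by clinician and site. *Methodological challenge #2* assigns variation in how treatment is delivered to secondary analyses. Neither section places clinician in the effectiveness comparison.

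**The concern.** The level of clustering that drove the sample size and the level named in the model are different. Site cannot stand in for clinician. Both sites are randomization strata and contain both arms, whereas the clinicians treat the bCBT arm only. Adjusting for site leaves the differences between clinicians within a site in the variance of the bCBT mean, but not in its estimated standard error.

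Clinician differences are plausible on the article's own account. Clinicians come from several disciplines, prior CBT skill does not affect their enrollment, no minimum skill is needed to stay in the trial, and modules are chosen jointly with the patient.

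If the model is run as written and clinicians do differ, the patients recruited to pay for clustering are counted as independent information. Intervals for bCBT versus usual care are then too narrow, and the error favours declaring bCBT effective. The depression, anxiety and cardiopulmonary outcomes of Objective #1 all rest on this comparison.

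**Working it through.** **Inputs from the article.** 180 patients before inflation; 25% attrition; 200 bCBT and 120 usual care; 12 clinicians; 2 sites; alpha 0.05.

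**Assumptions.** Two-sided test; 25% loss in each arm; equal caseloads; every evaluable bCBT patient is clustered; one outcome time point.

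**Step 1: can 320 be reproduced?** Not independently, because the inflation factor is not stated. Two back-solved readings both reach 320:
- *bCBT arm only, 180 planned as 90 per arm.* Usual care: 90/0.75 = 120. bCBT: 200 × 0.75 = 150 evaluable, and 150/90 = 1.667. Check: 90 × 1.667/0.75 = 200.
- *One factor on the total.* 320 × 0.75/180 = 1.333. Check: 180 × 1.333/0.75 = 320.

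**Step 2: variance of the difference, in units of the outcome variance.**
- Evaluable patients: 150 and 90. Per clinician: 150/12 = 12.5.
- Clinician ignored: 1/150 + 1/90 = 0.01778.
- Clinician counted: DE/150 + 1/90, where DE = 1 + (12.5 − 1) × ICC.
- Actual type I error: 2 × [1 − Φ(1.96 × r)], where r = √(0.01778 / variance with clinician counted).

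**Step 3: results by assumed ICC.**

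| ICC | DE | Variance with clinician | r | Type I error |
|---|---|---|---|---|
| 0 | 1.000 | 0.01778 | 1.000 | 5.0% |
| 0.01 | 1.115 | 0.01854 | 0.979 | 5.5% |
| 0.02 | 1.230 | 0.01931 | 0.959 | 6.0% |
| 0.05 | 1.575 | 0.02161 | 0.907 | 7.5% |
| 0.10 | 2.150 | 0.02544 | 0.836 | 10.1% |

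**Step 4: results under the two readings of 320.**
- DE 1.667 in the bCBT arm (ICC = 0.667/11.5 = 0.058): variance 1.667/150 + 1/90 = 0.02222; r = 0.894; type I error 8.0%.
- DE 1.333 in the bCBT arm (ICC = 0.333/11.5 = 0.029): variance 1.333/150 + 1/90 = 0.02000; r = 0.943; type I error about 6.5%.

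**Step 5: does adjusting for site help?** A simulation of 40,000 replicates placed 12 clinicians in two sites (7 and 5), with 150 bCBT and 90 usual care patients. It fitted site as a fixed effect and no clinician term. Rejection rates under no treatment effect were 4.9% at ICC 0, 6.1% at 0.02, 7.5% at 0.05, 8.2% at 0.058 and 10.3% at 0.10. These agree with the formula, so site adjustment does not remove the problem.

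**Step 6: power under the 1.667 reading.** 90 per arm gives 80% power at a standardized difference of (1.96 + 0.842) × √(2/90) = 0.418. With clinician counted, 150 and 90 evaluable patients again give 80% in the large-sample calculation. Ignoring clinician makes it look like about 88%.

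**The case against.** The strongest defence is that the model sentence names one level without excluding others. The full random-effects structure usually belongs in the statistical analysis plan, which is not shown and may include clinician. A reader might infer that the investigators decided to drop clinician, and the text does not show that. What remains is that the article does specify a nesting level, it is not the level used for planning, and nothing else puts clinician into the comparison. That is a conflict between two stated rules rather than a missing detail.

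Several other objections stand and limit the claim:
- The article speaks only of a potential for correlation. The ICC may be near zero, and it may differ between outcomes.
- The factor of 1.67 is not the plan's own figure. It assumes 1:1 planning of the 180 and inflation of one arm only, and the article gives another reason for the unequal split, namely to limit recruitment.
- Some bCBT patients will attend no session. If they are not clustered, the effect is smaller than computed.
- The calculation uses one time point, whereas the stated model is longitudinal.
- The article does not call this model primary, and it does not say that site is a random effect. A criticism that a site variance cannot be estimated from two sites would therefore be aimed at something not written.

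The promise to handle delivery variation in secondary analyses shows awareness of the issue, but it does not reach the main comparison.

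**Conclusion.** The concern holds in conditional form. The sample-size rationale and the stated model name different levels of clustering. With a positive clinician ICC, the model as written gives too small a standard error for bCBT versus usual care and a type I error above 0.05. Over ICC values from 0 to 0.10 the error runs from 5.0% to 10.1%. The two readings of the sample size in which the factor acts on the bCBT arm put it at about 6.5% or 8.0%. All these figures rest on the assumptions listed with the calculation.

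A reader might go further and conclude that standard errors will certainly be too small for every outcome, or that 8.0% is the error the plan itself implies. The article supports neither, since it gives no ICC and no inflation factor. The direction of the error is clear whenever the ICC is above zero, but its size is not known.

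**What to change.** In *Clinical effectiveness: analyses*, reconcile the model with the sample-size rationale:
- Add a clinician random effect in the bCBT arm only (a partially nested model), with a small-sample degrees-of-freedom correction because there are only about 12 clinicians.
- Keep site as a fixed stratification factor.
- State how bCBT patients who never attend are assigned, for example to the clinician of referral or as singletons.

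The choice of covariance across visits and of the particular correction can stay with the statistical analysis plan.

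The cost is a change of wording. Clinician identity is already needed for the planned comparison of engagement and adherence by clinician. Intervals widen by 1/r: about 4% at ICC 0.02 (1/0.959), 6% under the 1.33 reading (1/0.943), 12% under the 1.67 reading (1/0.894) and 20% at ICC 0.10 (1/0.836), plus a little for the degrees-of-freedom correction. The enlarged sample was meant to absorb this.
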